## Overview of the study

### Study Design and Participants

- **Type:** Nonblinded, randomized clinical trial.
- **Objective:** Evaluate standard supportive oncological care vs. early and systematic integrated palliative care in advanced cancer patients.
- **Exclusion:** Patients already receiving/had received palliative care.
- **Registration:** ClinicalTrials.gov (NCT03181854).
- **Duration:** September 2017 - October 2018.
- **Location:** 12 South Korean hospitals.
- **Recruitment:** Oncologists identified potential participants; both outpatients and inpatients were considered.

#### Inclusion Criteria:

1. Aged 20 or older.
2. Diagnosed with advanced solid tumor cancer (histologically/cytologically confirmed).
3. European Cooperative Oncology Group (ECOG) performance status: 0-2.
4. Estimated life expectancy of  $\leq 12$  months.
5. Consent to participate.

#### Exclusion Criteria:

1. Inability to speak/read Korean.
2. Poor health conditions, e.g., dyspnea, severe depression.
3. Not under current cancer treatment.
4. Received prior palliative care.

**Approval:** Institutional Review Board of Seoul National University College of Medicine and Hospital (H-1602-143-745).

### Procedure

The clinical research coordinator (CRC) explained study details to eligible participants. Upon physician's recruitment, participants provided written informed consent.

## **Randomization**

- **Method:** 1:1 ratio using a computerized random number generator (SAS 9.1.3; Proc plan).
- **Stratification:** Cancer type, age ( $< 65$  or  $\geq 65$ ), and enrollment hospital.

## **Intervention**

1. Initial meeting with palliative care team within three weeks post-randomization.
2. Self-study materials/videos provided on early palliative care/advance care planning (SMASH-based).
3. Telephone coaching: Weekly for the initial 12 weeks, then bi-weekly.
4. Symptom and psychological evaluation every three weeks for six months by the palliative care team.
5. Outpatient palliative care consultations according to a palliative care plan tailored to the patient's needs.
6. Symptom assessment every three weeks via MDASI and PHQ-2.
7. Control group: Usual oncological care with optional usual palliative care.

## **Palliative Care Team**

- **Members:** Palliative care specialist and health coach (nurses with  $>3$  years clinical experience) - depending on the hospital, some teams also included social workers.
- **Training:** 23 hours offline lectures, 14 hours tele-class coaching practice, and 3 additional hours by International Coach Federation certified coaches.

## **Measures**

- **Demographics:** Age, gender, education, employment, household income, residence.
- **Medical Information:** Tumor type/stage, ECOG status.
- **Primary Outcome:** Quality of life change over 24 weeks (via GHS/QOL scale of EORTC QLQ-C15-PAL).

- **Secondary Outcomes:** EORTC QLQ-C15-PAL functional/symptoms scales, MQOL functional scales, crisis-overcoming capacity (via SAT-SF).

## **Mortality Data Collection**

Family caregivers provided data on deceased patients. The survival data obtained from Statistics Korea (KOSTAT).

## **Data Analysis**

- 1) Survival analysis for two years post-enrollment using Kaplan-Meier curves.
- 2) Mean observed changes from baseline, adjusted differences in change scores at 12, 18, and 24 weeks were analyzed for survivors.
- 3) Effect sizes determined by standardized mean differences (Cohen's d), considering  $\geq 0.3$  as clinically relevant.

## Measurement

### 1) Measurement tools

| Measure                                                                         | Baseline | Week 12 | Week 18 | Week 24 |                                  |
|---------------------------------------------------------------------------------|----------|---------|---------|---------|----------------------------------|
| 1. Patient                                                               |          |         |         |         |                                  |
| General information                                                             | O        |         |         |         |                                  |
| Health-related quality of life indices
-EORTC QLQ-C15-PAL
-MQOL
-EQ-5D | O        | O       | O       | O       |                                  |
| Depression screening test (PHQ-9)                                               | O        | O       | O       | O       |                                  |
| Disease understanding                                                           | O        | O       | O       | O       |                                  |
| Strategy survey (competence of overcoming crisis) (SAT-SF)                      | O        | O       | O       | O       |                                  |
| Preference of documenting advance directives for life-sustaining treatment      | O        | O       | O       | O       |                                  |
| Quality assessment index (QCQ-EOL)                                              | O        | O       |         |         |                                  |
| Measure                                                                         | Baseline | Week 12 | Week 18 | Week 24 | 3 months following patient death |
| 2. Family                                                                |          |         |         |         |                                  |
| General information                                                             | O        |         |         |         |                                  |
| Quality of life of patient's family (CQOL-C)                                    | O        | O       | O       | O       |                                  |
| Quality of life index (MQOL)                                                    |          |         |         |         | O                                |
| Depression screening test (PHQ-9)                                               | O        | O       | O       | O       | O                                |
| Family's disease understanding                                                  | O        | O       | O       | O       |                                  |
| Strategy survey (competence of overcoming crisis) (SAT-SF)                      | O        | O       | O       | O       |                                  |
| Preference of documenting advance directives for life-sustaining treatment      | O        | O       | O       | O       |                                  |
| Cost-effectiveness analysis                                                     |          | O       |         | O       |                                  |
| Complementary alternative medicine                                              |          | O       |         | O       |                                  |
| Quality assessment index (QCQ-EOL)                                              |          |         |         |         | O                                |

## 2) Measurement procedure – Intervention Group

■ : PCT physician/ ■ : CRC or PCT nurse/ ■ : Both

|              |                                                         |                                                                                                                                                                                                                                                                                                                                                                                                                                                                                                                                                  |
|--------------|---------------------------------------------------------|--------------------------------------------------------------------------------------------------------------------------------------------------------------------------------------------------------------------------------------------------------------------------------------------------------------------------------------------------------------------------------------------------------------------------------------------------------------------------------------------------------------------------------------------------|
| INITIAL CARE | 1. Study registration and random assignment             | Once patients are referred by the treating department to register for the early palliative care research, they are briefly informed of the study and asked to sign a written consent form . Upon the completion of the Baseline Survey, random assignment is performed. Patients are provided with a copy of the early palliative care leaflet and educational materials (on early palliative care and advance care planning) and informed of the services to be provided later. PCT team consultation is scheduled. |
|              | 2. Registration and assessment prior to PCT examination | Prior to the PCT team consultation, the CRC (or PCT nurse) meets patients assigned to the Intervention Group. The Registration Form for Early Palliative Care Service, Global Assessment Form, and Summary Evaluation Form are filled out.                                                                                                                                                                                                                                                                                                |
|              | 3. Examination by PCT physician and paperwork           | The PCT physician performs an in-person examination based on the completed Patient Registration Form and Summary Evaluation Form. After examination, a Service Log entry is made. Subjects are registered on the website for the palliative care patient management program (PCT Web) and the Early Palliative Care Service Registration Form, Global Assessment Form, and Summary Evaluation Form are uploaded.                                                                                                            |
|              | 4. Establishment of advance care plan                   | At the weekly regular team meeting, advance care plans are established for patients newly registered for early palliative care service. (One PCT physician and one CRC [or PCT nurse] must be in attendance.)                                                                                                                                                                                                                                                                                                                             |
| ROUTINE CARE | 1. Follow-up                                            | The PCT physician performs regular in-person examinations (once every 3 weeks or once every 2 or 4 weeks if adjustment is necessary) by coordinating with the treating department's                                                                                                                                                                                                                                                                                                                                                              |

|  |                                          |                                                                                                                                                                                                                                                                                                                                                                          |
|--|------------------------------------------|--------------------------------------------------------------------------------------------------------------------------------------------------------------------------------------------------------------------------------------------------------------------------------------------------------------------------------------------------------------------------|
|  |                                          | 
schedule. (In-person examination is conducted based on the Global Assessment Form and Summary Evaluation Form filled out prior to the examination.)
 
The CRC (or PCT nurse) conducts surveys at weeks 12, 18, and 24. After examination, the Global Assessment Form, Summary Evaluation Form, and Service Log are uploaded to PCT Web.
        |
|  | ▼                                        |                                                                                                                                                                                                                                                                                                                                                                          |
|  | 2. Telephone coaching                    | 
A nurse who completed coaching training conducts telephone counseling weekly from week 1 through week 12, and bi-weekly from week 13 through week 24, using the counseling workbook to manage symptoms and assess the need for crisis intervention. A coaching log entry is made on the website for the palliative care patient management program.
 |
|  | ▼                                        |                                                                                                                                                                                                                                                                                                                                                                          |
|  | 3. Handover to the existing hospice team | 
If patients advance to an end stage and palliative care is the only treatment option, they are handed over to the conventional hospice team at the hospital and intervention is terminated. Although the intervention for early palliative care is terminated, follow-up surveys continue to be administered.
                                       |
|  |                                          |                                                                                                                                                                                                                                                                                                                                                                          |

|  |                              |                                                                                                                                                                                                         |
|--|------------------------------|---------------------------------------------------------------------------------------------------------------------------------------------------------------------------------------------------------|
|  | Visit at week 24             | Upon completion of the week-24 survey , the study is completed.                                                                                                                                  |
|  | In the case of patient death | 
If a patient dies, the Study Termination Form is filled out.
 
At 3 months after patient death, the family is contacted by phone to administer the 3-Month Post-Death Survey.
 |

*(Recommendations)*

|             |                        |                                                                                                                                                                                                                                                                                                                                                                                                                      |
|-------------|------------------------|----------------------------------------------------------------------------------------------------------------------------------------------------------------------------------------------------------------------------------------------------------------------------------------------------------------------------------------------------------------------------------------------------------------------|
| CRISIS CARE | 1. Crisis intervention | 
If a patient is admitted to ER, general ward, or intensive care unit, the CRC (or PCT nurse) visits the patient within 24 hours of admission, examines the crisis situation, and makes a PCT consultation request to the primary oncologist. The PCT team meeting should be held within 72 hours to establish a care plan (72 hours, i.e., 3 working days) is a recommendation). Meeting
 |
|-------------|------------------------|----------------------------------------------------------------------------------------------------------------------------------------------------------------------------------------------------------------------------------------------------------------------------------------------------------------------------------------------------------------------------------------------------------------------|

|  |                                                         |                                                                                                                             |
|--|---------------------------------------------------------|-----------------------------------------------------------------------------------------------------------------------------|
|  |                                                         | minutes on care planning are recorded and uploaded to the palliative care patient management program.                |
|  | ▼                                                       |                                                                                                                             |
|  | 2. Treatment consultation with other specialists | If interdisciplinary care is necessary, a request for treatment consultation is made to the appropriate specialists. |

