| 4 | Follow-up survey | CRC | 
 
• Administer follow-up surveys at weeks 12, 18, and 24.
 
• If a patient dies during the study period, contact the family by phone 3 months after the patient's death to administer a follow-up survey.
 
 | - Week 12, 18, and 24 Surveys
-3-Month Post-Death Survey |
|---|------------------|-----|------------------------------------------------------------------------------------------------------------------------------------------------------------------------------------------------------------------------------------------------------------------|-------------------------------------------------------------|

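### The protocol is inconsistent on who conducts the follow-up surveys and lets a member of the intervention team collect the patient-reported primary outcome in an open trial

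*Protocol*

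**What the plan says.** The Overview describes a "Nonblinded, randomized clinical trial". The primary outcome under Measures is "Quality of life change over 24 weeks (via GHS/QOL scale of EORTC QLQ-C15-PAL", and the table of measurement tools schedules that questionnaire at baseline and at weeks 12, 18 and 24.

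The protocol describes the collection of the post-baseline surveys in three places:

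- Measurement procedure – Intervention Group, Routine care, step 1: the CRC or, alternatively, the PCT nurse "conducts surveys at weeks 12, 18, and 24".
- Detailed study procedure, 4) Follow-up, step 4: the row reads "Follow-up survey | CRC", and the task is "Administer follow-up surveys at weeks 12, 18, and 24". The PCT nurse is not listed.
- Measurement procedure – Comparison Group, step 2: surveys are given at the same weeks, in the passive voice, with no collector named in the text.

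A note under the comparison-group procedure, and section 9) Additional items, let sites adapt team roles and PCT tasks. No section requires the survey collector to be independent of the patient's care. None says whether the patient fills in the form alone or staff read it out.

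**The concern.** The primary outcome is a subjective rating given by patients who know their arm. If the person who hands over or reads out the questionnaire also helps to deliver the care being tested, patients may answer more favourably out of courtesy or gratitude. Only intervention patients have a care relationship with the study team that the protocol itself creates, so such an effect would not be expected to cancel between arms.

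The analysis cannot repair this. The collector's relationship with the patient is a consequence of allocation, so adjusting for the collector would not separate it from a treatment effect. Because the protocol gives different answers on who collects, sites may also follow different rules.

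**Working it through.** The protocol states no sample size, standard deviation, alpha or power, so there is no figure to reproduce. The check is mainly a comparison of the text.

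**1. Is the CRC-only entry a real difference?** Yes. Other rows of the detailed procedure name the CRC and the PCT nurse together. Examples are the baseline survey and random assignment (section 1), the global assessment (section 2) and the preparation for examination (section 4, step 1). The follow-up survey row departs from that pattern.

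**2. Does the PCT nurse deliver the intervention?** Yes. The nurse is listed for the global assessment (section 2), the team meeting that sets care plans (section 3) and the crisis visit (section 6).

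**3. Is the CRC independent of care?** Not reliably. In the Intervention Group procedure the CRC may meet patients before the PCT consultation, attend the care-plan meeting and make the crisis visit. In the detailed procedure the CRC shares the global assessment (section 2) and the preparation for examination (section 4).

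**4. Who collects in the comparison group?** The text does not say. The actor legend offers the PCT physician or the CRC or PCT nurse, and its colour coding is not readable in the text at hand. As the legend has no category for the CRC alone, the colours could not settle the matter in favour of the CRC.

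**5. Can the survey fall on a day of PCT contact?** Yes. Examinations are nominally every 3 weeks, and 12/3 = 4, 18/3 = 6 and 24/3 = 8 are whole numbers. The Intervention Group procedure places its assessment forms before the examination but gives the survey no position.

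**6. What could a bias do? (illustration only)** Assume two means, 1:1 allocation (from Randomization: "1:1 ratio using a computerized random number generator"), two-sided alpha 0.05, SD = 1, a true effect of zero and a mean shift of b SD in the intervention arm. Then se = √(2/n), with n per arm, and

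P(reject) = 1 − Φ(1.96 − b/se) + Φ(−1.96 − b/se).

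The values n = 50 and n = 175 are assumed. The second is the n per arm for d = 0.3 at 80% power: 2 × (1.96 + 0.84)² / 0.3² ≈ 175.

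| b (SD) | n = 50 (se 0.200) | n = 175 (se 0.107) |
|---|---|---|
| 0 | 5% | 5% |
| 0.1 | 8% | 16% |
| 0.2 | 17% | 47% |
| 0.3 | 32% | 80% |

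For n = 50 and b = 0.1: b/se = 0.5, so 1 − Φ(1.46) + Φ(−2.46) = 0.072 + 0.007 = 0.079.

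The last row is the protocol's own relevance threshold (Data Analysis: "Effect sizes determined by standardized mean differences (Cohen's d", with 0.3 or more counted as relevant). Here b is an average over the whole arm. If only some patients are affected, it is the individual shift multiplied by their share. Nothing in the document fixes b.

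**The case against.** The case on the other side has real weight.

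- **The mismatch is mild.** The CRC is one of the two actors that the measurement procedure permits, and sites may adapt roles. This softens the conflict. It does not say who collects, and it adds no safeguard.
- **The form may already be self-completed.** The wording fits handing out a questionnaire, and patients who cannot read Korean are excluded. If so, an interviewer effect largely falls away and only a weaker social-desirability effect remains. This stands, but the protocol does not specify the mode.
- **Control patients may also know palliative care staff.** They can receive the institution's own palliative care on request, and some staff may serve both arms. This stands too, and the contrast between arms is therefore not absolute. The care relationship prescribed by the study still exists in the intervention arm only.
- **Survey order is often set in a site manual.** Agreed. Its absence here is not an error in itself.

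Three stronger readings are tempting but are not supported:

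- A reader might infer that intervention scores are in fact inflated. The protocol shows a route for bias, not its occurrence or size.
- A reader might infer that nurses collect in one arm only. The comparison-group text names nobody, and its legend includes the PCT nurse. What differs between arms is the care relationship, not a documented difference in collector.
- A reader might infer that the collector is also the coach, with 12 weekly plus 6 bi-weekly calls, 18 in all. The coaching text in the Intervention Group procedure begins "A nurse who completed coaching training conducts", so overlap is possible. Section 5) Telephone coaching, however, has the health coach turn to the PCT nurse as a separate role.

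**Conclusion.** The point holds as an inconsistency and a risk. The protocol permits a member of the intervention team to collect every post-baseline value of a patient-reported primary outcome in an open trial. It assigns the same task differently elsewhere, and in its text it leaves the collector in the other arm open. This may bias intervention-arm scores, probably upward.

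The size is unknown. The error rates above rest on assumed sample sizes and an assumed arm-wide shift, and they show only how sensitive the comparison would be if a shift existed. The conclusion does not depend on them. It rests on the conflicting text, the open design, the nurse's care role and the absence of any independence rule. The risk would be small if self-completion in private is already the practice.

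**What to change.** Reconcile the Intervention Group procedure, the Comparison Group procedure and section 4) Follow-up into one rule for both arms:

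- The patient completes the week 12, 18 and 24 survey privately, on paper or tablet, before any PCT contact that day.
- A CRC or other existing staff member hands it out and collects it. Where the site's staffing allows, this is someone who does not assess, coach or visit that patient.
- Where help with reading is given, record who gave it.

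Naming the CRC alone would remove the inconsistency but not the risk, because the CRC shares care tasks. Private self-completion is therefore the main safeguard, and it needs no extra staff. The cost is revised wording, a site instruction, some re-ordering of visits and, at some sites, reassignment of the hand-out task.
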